### **5.1.2 Allocation concealment mechanism**

The allocation sequence is implemented in the designated online platform. The result of randomization is communicated to the caregivers via internet after informed consent, screening, and entry of their baseline data. Randomization lists are only accessible to the technical administrators of the online platform.

### **5.1.3 Implementation**

Randomization lists per stratum are generated by IMBI staff not involved in the trial using R version 4.0.2 or higher and supplied to the technical administrators of the online platform. Participating caregivers enroll themselves into the trial during the online informed consent process and are automatically allocated online to one of the three arms using the caregiver's baseline data for stratification.

## **5.2 Blinding (masking)**

This is an open-label trial, therefore, there is no blinding, neither for participants nor for the study team.

## **6 Methods: Data collection, management and analysis**

### **6.1 Data collection methods**

#### **6.1.1 General Data**

By registration on the website the caregiver needs to fill in his/her e-mail-address and user name. Afterwards the caregiver will be asked some questions to check the in- and exclusion criteria (Screening). If the caregiver fulfils the criteria, he/she will be included in the study and asked, if the depressed person would like to participate as well. Then the caregiver will be asked for some general data including sociodemographic data of the caregiver and the depressed person, internet literacy, prior experience with psychoeducation as well as diagnostic and treatment status of the depressed person.

Before the intervention period starts the participant has to fill in the psychological questionnaires at T0 (see 0). If the depressed person participates as well, he/she will be asked to fill in a short questionnaire concerning his/her depressive symptoms. One week after starting the intervention (T1) the caregivers will be asked to fill in a short questionnaire concerning the psychological distress of the caregivers (K-10). After the intervention period of four weeks the caregivers and depressed persons fill in the psychological questionnaires again (T2). At this time there will be an additional questionnaire for caregivers asking for the acceptance, adherence and usage of the online program. All caregivers were also asked, if adverse events were occurring during the intervention period. Three months after T0 (T3) the caregivers and depressed persons will fill in the psychological questionnaires again und the caregivers will be asked for occurred adverse events in the last 8 weeks.

### 6.1.2 Psychological variables

The psychological variables will be collected by the following questionnaires (or interview), which the caregivers fill in (or participate in) at T0, T1 (only K-10), T2 and T3:

|                                                                  | Screening | T0 | T1 | T2  | T3  |
|------------------------------------------------------------------|-----------|----|----|-----|-----|
| Caregiver                                                 |           |    |    |     |     |
| informed consent                                                 | x         |    |    |     |     |
| Screening – questions concerning in- and exclusion criteria      | x         |    |    |     |     |
| sociodemographic data and relationship with the depressed person |           | x  |    |     |     |
| internet literacy                                                |           | x  |    |     |     |
| K-10                                                             |           | x  | x  | x   | x   |
| IEQ-EU                                                           |           | x  |    | x   | x   |
| SCL-K-9                                                          |           | x  |    | x   | x   |
| D-Lit                                                            |           | x  |    | x   | x   |
| FFB                                                              |           | x  |    | x   | x   |
| WHO-5                                                            |           | x  |    | x   | x   |
| acceptance, adherence and usages questionnaire                   |           |    |    | x   |     |
| adverse events questionnaire                                     |           |    |    | x   | x   |
| Qualitative interview                                            |           |    |    | (x) | (x) |
| depressed person (if applicable)                          |           |    |    |     |     |
| informed consent                                                 | x         |    |    |     |     |
| PHQ-9                                                            |           | x  |    | x   | x   |
| Qualitative interview                                            |           |    |    | (x) | (x) |

**K10 Scale:** The K10 scale (Kessler et al., 2002; German version: Giesinger, Rumpold, & Schüßler, 2008) assesses non-specific psychological distress during the past 30 days. It includes ten items on a five-point Likert scale and five additional items. The answer options for the first ten items range from one (none of the time) to five (all of the time). Questions begin with “During the last 30 days, about how often did ...” and continue with (1) ... you feel depressed (2) ... you feel tired out for no good reason? (3) ... you feel nervous?” The maximum score is 50, indicating high psychological

distress. Ten, the minimum score, indicates the absence of psychological distress. The additional items relate to the frequency of psychological distress in the past 30 days as compared to other times, the performance, the frequency of medical visits and the attribution of physical diseases on the perceived distress.

Giesinger et al. (2008) report good internal consistency of the scale (Cronbachs Alpha ranging from 0.80 – 0.90). To measure convergent validity, satisfactory correlations with related scales could be found (correlation with the State-Anxiety-Scale of the STAI (Laux, L., Glanzmann, P., Schaffner, P., Spielberger, 1981)  $r = .68$  and with the scale GSI of the BSI (Franke, 2000)  $r = .71$ )

**The Involvement Evaluation Questionnaire: The Involvement Evaluation Questionnaire:** The IEQ-EU (van Wijngaarden et al., 2000; van Winjgaarden, 1992) assessed the burden on caregivers of mentally ill people in the past four weeks. The present study used the German version of the IEQ-EU (Bernert et al., 2001). The IEQ-EU consists of 31 items, which are assessed on a five-point Likert scale ranging from “never” to “always”. Of the 31 items, 27 are grouped into four subscales, namely tension, supervision, worrying, and urging. The internal consistency (Cronbachs Alpha) of the subscales is reported as moderate or good, ranging from 0.71- 0.88, for the German version (Bernert et al., 2001).

**Symptom checklist 9-item short version:** The psychological burden on caregivers of mentally ill people was assessed by the German version of the SCL-K-9 (Klaghofer, R., Brähler, 2001) a shortened version of the Symptom Checklist 90-R (Derogatis, 1977; Franke, 1992). By using nine items on a five-point Likert scale ranging from 0 (not at all) to 4 (very severe), different psychological symptoms are assessed. Cronbach’s Alpha was  $\alpha = 0.87$ , which stands for a good reliability of the SCL-K-9 (Petrowski, Schmalbach, Kliem, Hinz, & Brähler, 2019).

**Depression literacy test:** The literacy concerning depression was assessed, using the German version of the Depression Literacy Test (D-Lit) (Freitag et al., 2018; english original: Griffiths, K.M., Christensen, H., Jorm, A.F., Evans, K., Groves, 2004). The D-Lit is a 35-item self-report questionnaire, assessing general information about depressive disorders, for example symptoms, impairments and treatments. Response options are “true”, “false” and “don’t know”. Reliability of the scale is reported as moderate with a Cronbachs Alpha of 0.75 (Freitag et al., 2018).

**Family Questionnaire:** The level of expressed emotion (EE) was assessed by the German version of the Family Questionnaire (FQ) (Wiedemann, Rayki, Feinstein, &

Hahlweg, 2002) a 20-item self-report questionnaire. On a four-point likert scale, ranging from “never” to “very often” caregivers of patients evaluate the frequency of specific reactions toward the patient. Internal consistency was excellent for the subscale “criticism” (Cronbachs Alpha ranging from 0.90- 0.92 depending on the sample) and good for the subscale “emotional over-involvement” (Cronbachs Alpha ranging from 0.79-0.82 depending on the sample).

**WHO-5:** The subjective psychological well-being was assessed by the German version of the 5-item World Health Organization Well-Being Index (WHO-5) (WHO, 1998). Response options are coded on a six point scale (0 = never; 5 = all of the time). The internal consistency of the German version of the WHO-5 is excellent (Cronbachs Alpha = 0.92) (Brähler, Mühlan, Albani, & Schmidt, 2007).

If the depressed person participates in the study as well, the person has to reply the following questionnaire at T0, T2 and T3:

**Patient health questionnaire:** Depressive symptoms were assessed by the German version of the patient health questionnaire (PHQ-9) (Löwe, B., Spitzer, R.L., Zipfel, S., Herzog, 2002; english original: Spitzer, 1999). Subjects indicated for each of the nine items on a four point scale, ranging from “never” to “nearly every day”, whether the symptom has bothered them during the previous 2 weeks.

The PHQ-9 showed excellent criterion validity (medical patients: sensitivity, 95%; specificity, 86%) an good internal consistency (Cronbachs Alpha = 0.88) (Gräfe, Zipfel, Herzog, & Löwe, 2004).

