## **4.3 Interventions**

Only the caregiver will receive one of the three interventions. If the depressed person participates as well, he/she only fills in a short questionnaire at each measurement point (and is able to provide additional feedback on the study if desired).

The online self-help program consists of four interactive, independently usable modules (Figure 1). It instructs caregivers on how to deal with common depressive

symptoms (module „Depression und Alltag“). Furthermore, it informs about depression as a mental illness, specific treatment options, critical situations and suicidal tendencies (module „Was muss ich wissen?“) and advises on how to strengthen the relationship between the depressed person and the caregiver (module „Beziehung stärken“). It provides instructions and exercises on how to find the right balance between caring for the depressed person and self-care (module „Selbstfürsorge“). Completing each module will take approximately 1.5 to 2.5 hours per module including homework exercises.

Fig. 1 Structure and modules of the online self-help program

[figure not shown]

During the study period of four weeks, the online self-help program will be offered in the following three individually randomized variants:

1) *Online self-help program with individual support*: The individual e-mail-support will be implemented by specifically trained psychologists and under regular supervision

with experienced psychotherapists. The psychologist contacts the caregivers three times per week via a secure message system, to give additional information about the modules (e.g. using examples), clarify individual content-related questions and strengthen the motivation of the caregivers in dealing with individual obstacles. For the supporting psychologists, guidelines with instructions and text templates will be developed, to reduce the expenditures of time and costs substantially. Because of its high degree of standardisation, the email-support is much more efficient than other possible formats (e.g. telephone or chat). Since many questions will arise repetitively, text templates will be created gradually, which will reduce personnel costs for the individual support.

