## **7 Methods: Monitoring**

### **7.1 Data Monitoring**

Following the guideline on data monitoring committees (European Medicines Agency [EMA]) Committee for Medicinal Products for Human Use [CHMP], 2005), neither a data monitoring committee nor interim analyses are considered necessary for this study, given the non-patient participants, short intervention as well as study time and low risk of harm expected from the intervention. The lead investigator will monitor the progress of the study with regard to the safety-relevant development as detailed in section 7.2.

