### **7.2 Harms**

The objective of this online-coach is to effect a positive change of caregivers' psychological burden and everyday life. Each change includes a risk for undesirable side effects. Side effects can be impacts on everyday life, interpersonal relationships (e.g. conflicts due to caregivers setting more boundaries towards the patients) and increased awareness of the burdens. Moreover, a temporary burden through the active analysis of actual stress factors is possible. For risk assessment (serious) adverse events ((S)AE) will be defined ahead of the study and recorded during the course of

studies. (Serious) adverse events are the occurrence or deterioration of psychiatric symptoms of the caregiver or the depressive person.

In case of a (S)AE there is an emergency button on the website of the online program, where the participant can find information and contacts of emergencies services and will be asked to contact them.

If (S)AE occur in the psychological message system contact or if participants contact a study member in case of an (S)AE, the lead investigator will be informed of the (S)AE immediately and will decide on the further procedure (e.g. study exclusion and outpatient or inpatient treatment recommendations).

For the following reasons, the intervention will be ceased in subjects of the study:

- Revocation of the subject's declaration of consent
- If, in the opinion of the lead investigator, further participation in the study would have harmful effects on the subject or the depressive person
- In case of new exclusion criteria
- If the emotional burden for the subject is too serious to cope with it himself, and intensive (professional) support is needed

Exclusion is decided by the lead investigators, in case of fulfilling one of the mentioned criteria. The reason for exclusion will be recorded. If needed, excluded subjects will be supported in searching further consulting or treatment. Also, if the subject revokes the informed consent, the subsequent reason will be recorded.

The lead investigator will monitor the progress of the study with regard to safety-relevant development. The lead investigator will discontinue the study, if:

- the cost-benefit ratio for the caregiver or the depressive ill person changes significantly
- there are indications, that the security of the caregiver or the depressive ill person is no longer guaranteed
- the continuation of the study is no longer justified by ethical or medical reasons

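### Adverse events are defined for both caregiver and depressed person, but only caregivers are asked about them, and the protocol states no safety use of K-10 or PHQ-9.

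*Protocol*

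**What the plan says.** Section 7.2 announces that "For risk assessment (serious) adverse events ((S)AE) will be defined ahead of the study" and then gives the content (opening bracket cut from the quote): "Serious) adverse events are the occurrence or deterioration of psychiatric symptoms of the caregiver or the depressive person". It sets no threshold and no criterion for seriousness.

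Section 6.1.1 describes the systematic questions. For T2: "All caregivers were also asked, if adverse events were occurring during the intervention period". For T3: "the caregivers will be asked for occurred adverse events in the last 8 weeks". Section 4.5 says the same.

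The table in section 6.1.2, introduced by "The psychological variables will be collected by the following questionnaires (or interview), which the caregivers fill in (or participate in) at T0, T1 (only K-10),", lists the adverse-event questionnaire at T2 and T3 in the caregiver block. The block for the depressed person holds consent, PHQ-9 (T0, T2, T3) and an optional qualitative interview. Section 4.3 agrees: "he/she only fills in a short questionnaire at each measurement point", with the option of further feedback on the study.

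For cases that must reach the lead investigator at once, section 7.2 names two routes: "If (S)AE occur in the psychological message system contact or if participants contact a study member in case of an (S)AE".

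K-10 is the primary outcome and PHQ-9 a secondary outcome (sections 4.4 and 6.3). Data review during the trial looks for programming errors and missing values (section 6.1.4).

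**The concern.** The event is defined in two people and the systematic question goes to one. If the protocol is followed as written, worsening in a participating depressed person enters the adverse-event record when that person volunteers it, when it surfaces in messages to a psychologist, or when the caregiver reports it. Adverse events in this group are then likely to be under-ascertained.

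The messaging route is also uneven. Two-way contact with a psychologist belongs to IND. AUT caregivers cannot reply to their messages, and sections 4.3 and 4.5 describe no messaging for TAU. A by-arm comparison of spontaneously reported events would mix true differences with differences in opportunity to report.

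Section 7.2 itself expects that some participants may be burdened by working through their stress factors. An improved mean K-10 can coexist with individuals who worsen. The trial collects scores that bear on this, but the protocol assigns them no part in describing harm.

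**Working it through.** **Who is covered and who is asked**

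| Item | Caregiver | Depressed person taking part |
|---|---|---|
| Inside the (S)AE definition (7.2) | yes | yes |
| Adverse-event questionnaire at T2 and T3 (6.1.1, 6.1.2) | yes | no |
| Symptom score | K-10 at T0, T1, T2, T3 | PHQ-9 at T0, T2, T3 |
| Stated use of that score (4.4, 6.3) | primary efficacy | secondary efficacy |
| Spontaneous report (7.2, 8.1) | yes | yes |
| Two-way psychologist messages (4.5) | IND only | none described |

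The second row is where the schedule and the definition part. The fourth row shows that the protocol names no safety use of either score.

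**What a deterioration count would look like**

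The protocol gives no figure to reproduce here. The following is an illustration; the cut-off is an assumption.

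Inputs: SD of K-10 change 6.2, midway in the range 4.6 to 7.8 (section 6.3.2); baseline SD also 6.2; Cronbach's alpha 0.80 to 0.90 (section 6.1.2), used in place of retest reliability, which is not given; 400:400:200 expected completers at T2 (section 4.6).

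1. Change beyond measurement error = 1.96 × SD × √(2(1 − alpha)).
   - alpha 0.90: 1.96 × 6.2 × √0.20 = 5.4 points.
   - alpha 0.80: 1.96 × 6.2 × √0.40 = 7.7 points.
   - On a whole-number scale this means a rise of at least 6, or at least 8.
2. Share of an arm with mean change 0 that reaches the cut-off (normal, continuity-corrected):
   - at least 6: 1 − Φ(5.5/6.2) = 18.8%, about 75 of 400.
   - at least 8: 1 − Φ(7.5/6.2) = 11.3%, about 45 of 400.
3. The same cut-offs with the protocol's outer SDs:
   - SD 4.6: 1 − Φ(5.5/4.6) = 11.6% and 1 − Φ(7.5/4.6) = 5.2%.
   - SD 7.8: 1 − Φ(5.5/7.8) = 24.0% and 1 − Φ(7.5/7.8) = 16.8%.
4. Precision of one active arm against TAU: half-width = 1.96 × √(p(1 − p)(1/400 + 1/200)).
   - p = 5%: 3.7 percentage points.
   - p = 11%: 5.3.
   - p = 19%: 6.7.

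No such calculation is possible for PHQ-9, because the protocol does not say how many depressed persons are expected to take part.

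**Which time points are usable**

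K-10 looks back 30 days (section 6.1.2). T1 is one week after randomisation, so 30 − 7 = 23 of the 30 days lie before it. At T2, after four weeks, 28 of the 30 days lie after randomisation. T2 and T3 are therefore informative about deterioration under the assigned condition; T1 mostly is not.

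**The case against.** **Other routes exist.** A reader might infer that harm is recorded only on the caregiver form, or that the depressed person's worsening counts only if the caregiver reports it. Neither is right. Section 7.2 lets participants contact a study member, section 6.1.5 includes depressed persons among participants, section 8.1 offers telephone contact, and section 4.3 allows feedback. The caregiver form may also ask about the depressed person by proxy; its content is not given. What stands is that this person is not systematically asked.

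**A rule may exist elsewhere.** Section 7.2 promises a definition of (S)AEs ahead of the study, and section 6.3.1 leaves analytic detail to the SAP. The finding is only that the protocol states no safety use of the scores. The deterioration table could well sit in the SAP. The form schedule could not: the protocol fixes it, and the SAP may be completed as late as the blinded review of the trial data, which may be too late to add a question.

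**The scores are imperfect.** It is tempting to call K-10 and PHQ-9 unbiased, direct measures of harm. They are self-reports in an open-label trial, K-10 measures non-specific distress, about 20% of K-10 values are expected to be missing at T2, and PHQ-9 covers only depressed persons who take part. Their merit is the same schedule in every arm.

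**The monitoring waiver.** Section 7.1 states that "neither a data monitoring committee nor interim analyses are considered necessary for this study, given the non-patient participants". A reader might infer that this misdescribes a trial that also measures depressed persons. The text does not support that: only caregivers receive an intervention (section 4.3), and section 7.3 explains the phrase as meaning caregivers. Section 7.1 also relies on the short duration and low expected risk.

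**Conclusion.** The point holds as a mismatch between the people in the (S)AE definition and the people systematically asked, together with an uneven spontaneous route and no stated safety use of scores already collected. It does not show that harms will be missed altogether, and it leaves the power and the primary analysis untouched.

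The size of under-reporting cannot be estimated from the document. The illustrative 11% to 19% (5% to 24% over the protocol's SD range) is not a count of missed harms: it arises with no mean change at all, from natural fluctuation and measurement error. It assumes normal changes on a scale bounded at 10 and 50, internal consistency in place of retest reliability, and a cut-off that the protocol does not contain. Only the difference from TAU carries information, and the trial would estimate it to within roughly 5 to 7 percentage points at those central rates.

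**What to change.** 1. Add the adverse-event item to the participating depressed person's existing T2 and T3 form, and amend sections 4.3, 4.5, 6.1.1 and 6.1.2 to match. State whether the caregiver form also asks about the depressed person.
2. Add a descriptive safety outcome by arm: number and proportion of caregivers with K-10 deterioration from T0 at T2 and at T3, and of participating depressed persons with PHQ-9 deterioration from T0 at T2 and at T3. Fix the cut-offs before unblinding. Report risk differences with 95% confidence intervals and the number missing per arm. Leave out T1 for the recall reason above.
3. When adverse events are reported by arm, give the route by which each was found, so that the messaging difference is visible.

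The cost is one online item, a protocol amendment and a short table; no new assessments are needed. The drawback is that the counts include natural course and measurement error, so they must be read against TAU. Whether any score should prompt clinical action is for the sponsor to decide.
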